### Intervention

Informed by the UK Medical Research Council “Framework for design and evaluation of complex interventions to improve health” [32], the aim of the intervention is to enhance identification and linkage to HCV care and treatment among patients attending primary care for OST and includes the following (see Figure 1):

Outreach of an HCV-trained liaison nurse into GP practicesIn-practice education for GPs and practice staff regarding developments in diagnosis and treatment of HCVEnhanced access of patients to community-based evaluation of HCV disease, including a novel approach to diagnosis, that is, transient elastography (Echosens FibroScan Mini 430)Researcher-facilitated practice audit of HCV care processes and feedback to GP

### Data Collection

Data on patient demographics and HCV care processes/outcomes will be extracted from the patient’s clinical electronic or paper medical record and also from patient self-reported data collected through the HCV liaison nurse assessment to include the following:

Prior HCV testingHCV status—antibody and Ribonucleic Acid (RNA) or antigenReferral and attendance for HCV care at a hospital’s Department of Hepatology or Infectious DiseasesHCV assessment and treatment and sustained virological response (SVR)Alcohol screening and brief intervention using a validated alcohol screening instrument (eg, AUDIT)Other blood borne virus (BBV): HIV and hepatitis B virus (HBV)BBV testing/vaccination: liaison nurse will assess if the patient has been tested for HCV, HIV, and whether HBV immunization is requiredChronic illnessMortality

**Figure 1 figure1:**
[figure not shown]
Flowchart of the nurse-led intervention. GP: general practitioner; HCV Ab: HCV antibody; HCV: hepatitis C virus; ID: infectious diseases; MMUH: Mater Misericordiae University Hospital; PCR: polymerase chain reaction; OPD: Outpatient Department; OST: opiate substitution therapy; RNA: Ribonucleic Acid; Ag/RNA: Antigen/Ribonucleic Acid.

The HCV liaison nurse will meet and assess the patient, addressing any questions they may have regarding their HCV status. The liaison nurse will also gather data on the following variables:

HCV risk factors (eg, incarcerated, tattoos, piercings, blood transfusion, sexually transmitted infection test)OST treatmentAlcohol use assessed using the AUDIT questionnaireHCV testing, assessment, and treatment historyOther BBV testing and HBV and hepatitis A virus vaccination historyQuality of life (EQ5D-3L)—collected by HCV liaison nurse just before their assessment and intervention where necessary with each patientHCV-antibody positive and Ribonucleic Acid/Antigen (RNA/Ag) status (positive or unknown)Echosens FibroScan Mini 430 data (the nurse will have received Echosens FibroScan Mini 430 training)

After the assessment, the liaison nurse will provide the patient with information/education regarding HCV, including how it is transmitted and how to prevent transmission. Harm reduction strategies will also be addressed if required. A handover of the nurse’s assessment will be given to the GP. HCV Ab+ patients will be referred to specialist services if they are Ag+, RNA+, or if Ag and RNA status are unknown. This process will be carried out by the GP with the assistance of the HCV liaison nurse. Referrals are submitted to the hospital’s Hepatology or Infectious Diseases department.

### Qualitative Data Collection

Semistructured interviews will be conducted by a member of the research team with health care professionals (n=12) and patients (n=12; or until analytical saturation is reached) at follow-up, purposively sampled from recruited practices and patients. Interviews will be guided by an interview schedule informed by our previous feasibility study in Irish primary care [33], including participants’ lived experiences of HCV including barriers and facilitators to treatment, as well as questions exploring participants’ experiences and acceptability of the study intervention. With purposive sampling, the researcher samples particular settings, persons, or events deliberately selected for the important information they can provide that cannot be acquired as well from other choices [34]. In line with the simultaneous analysis and collection of data that is an integral part of qualitative analysis, after the first 3 health care professional and first 3 patient interviews, recruitment will be informed by themes identified in the data. Participants recruited for the qualitative data collection will be provided with an amended participant information leaflet outlining the purpose of this part of the study, and, if agreeable, asked to sign a separate consent form.

### Outcome Measures

To establish the feasibility, acceptability, and likely efficacy of this intervention in practice, the following outcome measures will be examined (see Table 1 for measures to establish feasibility, acceptability, and likely efficacy):

Primary outcomes include the following:

Proportion of participants who have been screened for HCVProportion of HCV antibody–positive patients commenced on/completed antiviral therapy/achieved SVR

Secondary outcomes include the following:

Proportion of those screened who tested HCV antibody positiveProportion of HCV-positive patients who have been assessed by Echosens FibroScan Mini 430Proportion of HCV-positive patients who have been referred to specialist hepatology or infectious diseases serviceProportion of HCV-positive patients who have attended specialist hepatology or infectious diseases serviceProportion of HCV-positive patients received an alcohol screening brief interventionProportion of participants tested for anti-HIV antibody, anti-HBc (hepatitis B core) antibody, or hepatitis B surface antigen (HBsAg)Proportion of participants immunized against hepatitis B/A virusExperience and evaluation of the intervention among key informants (GPs, nurses, and patients)Number of patients attending general practice for OST postintervention for follow-up testingEvaluate feasibility and possible efficacy of intervention by comparing pre-post intervention dataEvaluate the cost-effectiveness of the interventionCompare GPs’ and practice nurses’ knowledge and attitudes and practice pre-post intervention

### Data Analysis

Quantitative data will be analyzed using SPSS v22. Questionnaires will be summarized using descriptive statistics, and a pre-post intervention analysis will be performed using Fisher exact test.

Semistructured interview transcripts will be checked for accuracy and then imported into NVivo10 qualitative data analysis software to aid management and analysis of data. Analysis will begin shortly after data collection starts and will be ongoing and iterative. Analysis will inform further data collection; for instance, analytic insights from data gathered in earlier interviews will help identify any changes that need to be made to the topic guide during later interviews. Thematic analysis [35] using a data-driven inductive approach will be used to scrutinize the data to identify and analyze patterns and themes of particular salience for participants and across the dataset. The first author (a social psychologist with extensive experience in using qualitative methodologies) will analyze and code the data. The data will also be independently analyzed by the second author who also has extensive expertise in qualitative research. Final themes will be agreed between the 2 authors, and the last author will audit the final analysis.

The goals of this study are to examine feasibility, acceptability, and likely efficacy of the intervention. Descriptive statistics will be analyzed with respect to key feasibility variables. The qualitative analysis of patients’ and health care professionals’ experiences of the intervention will be used to assess acceptability. Although the study is not designed to determine effectiveness, we will examine likely efficacy by comparing process and outcome measures, which will allow estimation of the intracluster correlation coefficient and thus inform the sample size of a possible future definitive trial.

**Table 1 table1:** Measures to establish feasibility, acceptability, and likely efficacy.

Aim	Patient level	Practice level
Feasibility	Compare pre-post intervention data on patient demographics, hepatitis C virus (HCV) care processes and outcomes extracted from patients’ clinical electronic or paper medical records, and also from patient self-reported data collected through the HCV liaison nurse assessment; patient recruitment rates; patient retention level; and cost-effectiveness of the intervention	Compare pre-post intervention data on patient demographics, HCV care processes and outcomes extracted from patients’ clinical electronic or paper medical records, and also from patient self-reported data collected through the HCV liaison nurse assessment; practice recruitment rates; practice retention level; cost-effectiveness of the intervention
Acceptability	Patients’ experience of intervention evaluated by analysis of semistructured interviews with patients	GPs’^a^ and practice nurses’ experience of intervention evaluated by analysis of semistructured interviews with patients
Likely efficacy	Although not adequately powered to examine efficacy, possible efficacy will be assessed by proportion of patients who have been screened for HCV and alcohol use, proportion of patients who have been referred for treatment (HCV, alcohol), and cost-effectiveness of study	Although not adequately powered to examine efficacy, possible efficacy will be assessed by knowledge and attitudes and practice pre-post intervention and cost-effectiveness of study

^a^GP: general practitioner.

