### Study Population

A sample of 24 OST-prescribing GP practices will be recruited from the professional networks of members of the research consortium.

Practices will be eligible to participate if they are registered to prescribe methadone and have at least 10 patients currently receiving OST; agree to participate in practice audit; and (3) agree to facilitate nurse liaison.

Patients (n=240) will be eligible to participate if they are on OST (ie, methadone); are aged at least 18 years; and attend the practice for any reason during the recruitment period.

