### Approach to Sampling and Recruitment

A standardized nonprobability sampling framework will be used to identify 10 consecutive patients from each practice or center to participate in the study. On the basis of the recommendations for good practice in feasibility studies [30] and our previous work conducting feasibility studies with PWID [29,31], we estimate that 240 patients (attending 24 general practices) will be adequate to calculate the actual recruitment and retention rates (ie, feasibility) and provide data on acceptability of study processes and outcome measures, which will inform a future definitive trial. This approach to recruitment reflects the challenges involved in recruiting this population group for projects. Patients who consult a doctor or nurse in participating practices or centers and who are eligible for the study will be given written information and a verbal explanation of the study, including the study purpose, procedures, and how findings will be utilized. Those who are interested in participating will be asked to sign a consent form, which will be witnessed by the doctor or nurse or the researcher. Although the initial approach to participate will be from a health care professional, recruitment will be facilitated by a member of the research team being “on site” to support the practice during the recruitment phase and answer any questions potential participants may have. The recruitment phase will involve each participating practice engaging in an intensive, 4-week period of patient recruitment, an approach we found most effective in previous work with this population [28,29]. During this 4-week period, the member of the research team will aim to (1) obtain contact details for and informed consent from eligible patients, (2) review the clinical records of patients who consent to participate in the study, and (3) collect baseline data, including patient demographics and current care process and outcome measures from clinical records.

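### Fisher's exact test, the only pre-post test named, is a poor fit for the GP and practice nurse knowledge and attitude questionnaire: it ignores the pairing of answers and, if the instrument is scored, the grading too

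*Protocol article*

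**What the plan says.** The Data Analysis section of the protocol article gives one sentence on quantitative testing: "Questionnaires will be summarized using descriptive statistics, and a pre-post intervention analysis will be performed using Fisher exact test". No other inferential test appears in the article.

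The practitioner questionnaire enters in two places. Outcome Measures lists, among the secondary outcomes, a comparison of GPs' and practice nurses' "knowledge and attitudes and practice pre-post intervention". Table 1, in the practice-level cell for likely efficacy, says that "possible efficacy will be assessed by knowledge and attitudes and practice pre-post intervention and cost-effectiveness of study", and the same cell states that power for efficacy is inadequate.

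On size, Study Population says "A sample of 24 OST-prescribing GP practices will be recruited". The number of GPs and nurses who will complete the questionnaire is not given. Nor are its items, response format, scoring or any cut-point. The article also limits its own ambition: "Although the study is not designed to determine effectiveness, we will examine likely efficacy by comparing process and outcome measures".

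**The concern.** Fisher's exact test takes a table of counts from independent groups. Both primary outcomes and most secondary outcomes are proportions, so the categorical form suits their data type. A practitioner questionnaire differs in two ways.

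- **Pairing.** A before-and-after comparison of the same GPs and nurses gives two answers per person. Fisher's test treats them as coming from different people. This applies to any response format.
- **Scale.** Knowledge is often summed over items, and attitudes are often recorded in ordered grades. If so here, Fisher's test either needs the score to be cut or treats ordered categories as unordered.

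Apart from cost-effectiveness, this comparison is the only practice-level sign of likely efficacy in Table 1, and it is a natural readout of the in-practice education component. The number of respondents is probably small, so information is worth keeping. A Fisher p-value also gives no mean change or confidence interval to describe what the education achieved.

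**Working it through.** **The plan's own figure.** The only sample-size figure is for patients: 24 practices × 10 patients = 240, which agrees with the article. It does not bear on the practitioner questionnaire, for which there is no stated figure to reproduce. Everything below rests on assumptions.

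**Assumed inputs.** 24 to 48 practitioners (one or two per practice, 24 × 1 to 24 × 2), each measured twice; normal underlying score with SD 1; true shift 0.5 SD; pre-post correlation 0.5; cut at the baseline median; two-sided 5%.

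**Why pairing matters.** The SD of a within-person change is √(2(1 − 0.5)) = 1.0. With n = 24 its standard error is 1/√24 = 0.204. A comparison that treats the two occasions as independent uses √(2/24) = 0.289. The same 0.5 shift is therefore 0.5/0.204 = 2.45 standard errors when paired and 0.5/0.289 = 1.73 when unpaired. The unpaired analysis errs on the conservative side: in simulation with no true change, Fisher rejected in 0.8%, 0.6% and 0.7% of runs at n = 24, 36 and 48, against a nominal 5%.

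**Power by simulation, ungrouped score** (4,000 runs; Monte Carlo standard error at most √(0.5 × 0.5/4,000) = 0.8 points):

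| n | Fisher, median cut | Exact McNemar, same cut | Unpaired t, full score | Paired t, full score |
|---|---|---|---|---|
| 24 | 15% | 22% | 36% | 65% |
| 36 | 25% | 39% | 57% | 84% |
| 48 | 38% | 54% | 74% | 93% |

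**Same inputs, score rounded to 10 steps.** Fisher after the cut: about 16% (n = 24) and 36% (n = 48). Unpaired rank test on the score: 34% and 68%. Paired t-test: 62% and 90%.

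**Splitting the gap (10-step score).** Keeping the score but staying unpaired gains 34 − 16 = 18 points at n = 24 and 68 − 36 = 32 at n = 48. Adding the pairing gains a further 62 − 34 = 28 and 90 − 68 = 22. The split depends on the order of correction. At n = 24, pairing first takes Fisher from 16% to 23% (exact McNemar), a gain of 7, and restoring the score then adds 62 − 23 = 39. Both sources contribute either way.

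**If nothing needs to be cut.**

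- *Natively binary item, 50% correct rising to 75%, phi 0.5.* Fisher against exact McNemar: 27% against 53% (n = 24), 49% against 83% (n = 36), 70% against 95% (n = 48). For a single item the whole shortfall is pairing.
- *Five-level response in an uncut table* (1,500 runs, 0.5 SD shift, correlation 0.5). An r × c exact test against a rank test, both unpaired: 15% against 32% (n = 24) and 37% against 67% (n = 48). Avoiding the cut recovers almost nothing over the 2 × 2 version (15% and 39%), because order is still ignored.

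**The case against.** The strongest objection is that the article never describes the instrument. A reader might infer that knowledge and attitude scores must be cut into categories. The documents do not support that: items may be correct/incorrect or yes/no from the start, and multi-level answers can enter a larger table uncut. This stands, and it makes the scale part of the point conditional. It does not touch the pairing part.

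Second, the sentence has two clauses. Questionnaires could be summarised descriptively only, with Fisher kept for the patient proportions. That reading is possible, and under it score means and changes could still be reported, so one cannot say that the plan yields no mean change. But Table 1 counts the pre-post questionnaire comparison as evidence of likely efficacy, and the article says, without restriction, that "a pre-post intervention analysis will be performed using Fisher exact test". The sentence needs clarifying on either reading.

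Third, a reader might infer that a real improvement will probably be reported as no change. The assumed figures do not show this in general. With 48 practitioners and a 0.8 SD shift, Fisher after a median cut has about 87% power. With 24 and a 0.5 SD shift, the unpaired rank test on the full score has only about 34%, so a miss is likely even without a cut. Likewise, a respondent count of a few dozen is an inference from 24 practices.

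Fourth, the outcome is secondary, declared underpowered, and set in a feasibility study. A condensed article may leave scoring to a fuller document. That also stands: the missing instrument details are no fault. What remains is a method that the article does state and that fits this comparison poorly.

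**Conclusion.** The point holds in conditional form. Fisher's exact test is the only pre-post test named and, read naturally, it covers the practitioner questionnaire. It ignores the matching of answers from the same practitioners in any format and, if the instrument is graded or summed, the ordering as well.

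Under the assumptions above, power is about 16-36% with Fisher after a median cut and 62-90% with a paired t-test on the score, with an unpaired rank test between at 34-68%. These figures show the order of magnitude of the loss. They are not estimates for this study, because respondent number, scale, shift and correlation are all assumed. The pairing part further assumes that the same people answer on both occasions, which the design implies but the article does not spell out.

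The importance is minor: the outcome is secondary and exploratory, and no primary conclusion depends on it.

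**What to change.** Amend the Data Analysis sentence as follows:

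- Limit Fisher's exact test to categorical comparisons of independent groups.
- Where the practitioner questionnaire gives knowledge or attitude scores, report the within-practitioner mean change with a 95% CI. Use a paired t-test, or Wilcoxon signed-rank if the changes are skewed, and a practice random effect where a practice has more than one respondent.
- For binary items, use a paired test such as McNemar.
- Keep item percentages as description.

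The cost is about one sentence and standard procedures, with no new participants or visits. The before and after forms must be linkable by respondent. The article already assigns a code to each participant's data and counts GPs as participants under Ethical Considerations, so it need only confirm that this covers practice nurses. The small downside is that a score change is less direct to read than a percentage, which is why the item percentages should stay.

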## Methods

### Study Design and Setting

This is a prospective, nonrandomized, pre-post intervention feasibility study to be conducted in OST-prescribing general practices from three sites across the Hepcare Europe consortium (Dublin, London, and Seville). Practices will be given written information on the study and asked to indicate their interest in participating. Our recent experience recruiting general practices [28,29] has taught us the importance of a researcher promptly following up an expression of interest from a GP to fully explain the study and highlight what will be required from the GP in terms of time and commitment to the study. As such, practices who express an interest in participating will be contacted by a member of the research team to explain the aims of the study and what is required.

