### Ethical Considerations

The study has been approved by the Mater Misericordiae University Hospital Research Ethics Committee (Ref: 1/378/1722) and the Research Ethics Committees of the collaborating institutions in London and Seville.

Ethical considerations and safeguards include the following:

Informed consent and consenting capacity: all potential participants (GPs, patients) will be given written information on the study, the model of care being proposed, and asked to provide written consent that they are happy to participate and that nonparticipation will not compromise their usual care. Participation in the study will be on a voluntary basis. No inducements to participate will be offered.Confidentiality: Any data/personal details that could potentially reveal the identity of individuals will be removed. Only anonymized, deidentified information will leave the practice of origin. To allow follow-up, an alphanumeric code will be assigned to each participant’s data; a database will be maintained on a password-protected database at Mater Misericordiae University Hospital. The list will be kept separately from patient data but will indicate the medical record number of each participant and the alphanumeric code. All research data will be stored on a password-protected desktop computer at the host organization. Study participants will be invited to give permission to have their name, address, and contact details held by the research team to facilitate their receiving a synopsis of the study findings on publication and to be contacted for follow-up data collection. All data will be stored securely at the host institution.Clinical governance, do no harm: it is possible that participating in the study may raise health-related issues for participants and may identify a health issue that requires a clinical intervention. Therefore, all participants will be advised to speak with their doctor if participating in the study has raised any such issues. At the conclusion of the intervention, the HCV-trained liaison nurse will conduct a handover of clinical information to the GP, which includes recommendations for follow-up care.

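### Fisher's exact test does not suit the pre-post comparison of patient outcomes: one followed cohort in 24 practices is analysed as two independent samples

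*Protocol article*

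**What the plan says.** The Data Analysis section states that "a pre-post intervention analysis will be performed using Fisher exact test". The same sentence opens with descriptive summaries of questionnaires, so the intended scope of the test is not quite clear, but no other test is named anywhere in the article.

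Other sections describe the data to be compared:

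- Study Design and Setting calls it a "prospective, nonrandomized, pre-post intervention feasibility study". There is no control group.
- Approach to Sampling and Recruitment plans to "identify 10 consecutive patients from each practice or center", giving 240 patients in 24 practices. The researcher will then "collect baseline data, including patient demographics and current care process and outcome measures from clinical records" for those who consent.
- Ethical Considerations: "To allow follow-up, an alphanumeric code will be assigned to each" participant's data.
- Table 1 lists patient retention as a feasibility measure.
- Data Analysis expects that comparing process and outcome measures is something "which will allow estimation of the intracluster correlation coefficient", for planning a later trial. It does not connect this to the pre-post test.

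**The concern.** Fisher's exact test compares two independent groups of independent observations. Here the before and after values for a patient outcome belong largely to the same people, and those people sit ten to a practice under an intervention that works partly at practice level (staff education, audit and feedback, nurse outreach).

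The two departures act in opposite directions. When the test ignores the pairing, it counts stable differences between patients as noise in the change, so it is too conservative and any independent-samples interval is too wide. When it ignores change shared by patients of one practice, it overstates the information in 240 patients and can reject too often.

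What is at stake is the precision and the p-values attached to likely efficacy, not the estimated proportions.

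**Working it through.** **Inputs from the article.** 24 practices × 10 patients = 240, which reproduces the stated sample size. The article has no power calculation to reproduce. It gives no baseline rate, effect size, significance level, intracluster correlation or pre-post correlation.

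**Assumptions for illustration.** Two-sided 5% level, no dropout, and the rates shown below.

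**1. Effect of ignoring the pairing.** Suppose 180/240 (75%) are screened before and 192/240 (80%) after, with 12 gains and 0 losses. The change is d = 12/240 = 0.05.

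- Independent-samples SE: √(0.75 × 0.25/240 + 0.80 × 0.20/240) = √(0.000781 + 0.000667) = 0.0381. The 95% CI is 0.05 ± 1.96 × 0.0381, or −2.5 to 12.5 points.
- Paired SE: √[((gains + losses)/240 − d²)/240] = √[(12/240 − 0.0025)/240] = √(0.0475/240) = 0.0141. The 95% CI is 2.2 to 7.8 points.
- Fisher's exact test on 180/240 against 192/240: p = 0.229.
- Exact McNemar: 2 × 0.5¹² = 0.0005. This shows what the pairing contributes and is not a recommended main test.

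From a 75% baseline Fisher needs 19 newly screened patients to reach p < 0.05 (18 gives 0.058, 19 gives 0.043).

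Fisher's result does not depend on how the pairs fall. For 168/240 to 182/240 it gives p = 0.18 in every case. The independent SE is 4.05 points. The paired SE is 1.51 points with 14 gains and 0 losses, or 2.40 points with 24 gains and 10 losses.

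**2. Direction of the error once practices are considered.** Simulation with no true average change, 24 × 10 patients, 70% at both times, an underlying normal scale with total variance 1, a stable practice share of 0.05, and 5,000 runs per row:

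| Stable patient share | Practice-by-period share | Fisher, false positives | Practice-level paired t test |
|---|---|---|---|
| 0.5 | 0 | 0.011 | 0.046 |
| 0.8 | 0 | 0.001 | 0.051 |
| 0.3 | 0.05 | 0.045 | 0.053 |
| 0.5 | 0.15 | 0.082 | 0.048 |
| 0.3 | 0.15 | 0.102 | 0.048 |
| 0.1 | 0.30 | 0.195 | 0.050 |

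A rerun with a different seed gave the same pattern. Fisher is well below 5% when practices share no change, close to 5% with a little shared change, and above it when shared change is strong. The last row is an extreme assumption. The practice-level paired analysis stays near 5% in every row.

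A stable difference between practices largely cancels in a within-patient comparison. The usual design effect 1 + 9 × ICC therefore does not carry over; what matters is how much the *change* varies between practices.

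**3. Limit of the simulation.** It treats the outcome as reversible. Several listed outcomes read as cumulative (having been screened, referred or immunised). For these, losses cannot occur, a null of no change says little, and the size of the change with its interval is the useful result.

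**The case against.** The strongest reply is that this is a feasibility study. Data Analysis says that it is not designed to determine effectiveness, and Table 1 says that it is not adequately powered for efficacy. No success threshold or progression rule depends on the p-value. Feasibility is assessed descriptively and acceptability qualitatively, and estimating the ICC does not need the test. All of this stands and limits the seriousness of the point. It does not make the test suitable: comparing pre-post data is a listed outcome, and the Conclusions section promises early indications of whether the model is effective.

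Three stronger readings go beyond the documents:

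- *A reader might infer that the p-values are uninterpretable, or that Fisher is inflated here.* Neither is shown. With moderate variation in change between practices (a probit SD of 0.4, assumed), Fisher's false-positive rate is about 2% to 5%. It is the exact McNemar test, which keeps the pairing but ignores practice, that rises to about 9% to 12%. Fisher exceeds 5% only under stronger assumed sharing.
- *A reader might infer that every outcome compares the same 240 people.* The second primary outcome and several secondary ones are restricted to antibody-positive or HCV-positive patients. Screening can enlarge that set, so the before and after groups may overlap only partly.
- *A reader might infer that the GP and nurse questionnaires are paired too.* The article says only that staff knowledge, attitudes and practice are compared before and after. The participant code is tied to a medical record number, so it does not show that staff forms are linked.

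The scope of the Fisher sentence is also ambiguous. If it covers only questionnaires, the article names no test for the patient outcomes and the point about them falls away; the sentence would then need only to say so.

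**Conclusion.** The point holds for patient outcomes, reading the Fisher sentence as covering them. The stated test assumes independent samples, while the article describes a linked cohort clustered in 24 practices. In the 180/240 to 192/240 illustration the independent-samples SE is 0.0381/0.0141 = 2.7 times the paired one. With losses as well as gains (24 and 10 in the second example) the ratio is 4.05/2.40 = 1.7. If change is strongly shared within practices, the error runs the other way. All rates and correlations are assumed, and the article gives nothing that settles the direction.

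This should be fixed but does not threaten the study: point estimates, recruitment, retention and the qualitative work are unaffected, and no power for efficacy is claimed.

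**What to change.** For patient outcomes, replace Fisher's exact test with the pre-post risk difference and a 95% confidence interval that respects pairing and practice clustering. Either of these would do:

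- A practice-level paired analysis: for each practice take the after proportion minus the before proportion, then use the mean of the 24 differences with SE = SD/√24 and a t distribution on 23 degrees of freedom.
- A GEE of the outcome on period, with practice as the cluster and a small-sample correction for 24 clusters.

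State the before and after denominators for outcomes restricted to HCV-positive patients, and how patients who enter that group between the two times are handled.

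Do not make McNemar the main test. It ignores practice clustering, and it is uninformative for cumulative outcomes, where six new events with no possible losses already give p = 2 × 0.5⁶ = 0.03. A logistic model with a patient effect would be unstable for the same reason.

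Use a paired method for the GP and nurse questionnaires only if the same staff members' forms are linked; otherwise say that they are not. Make clear which data each method covers.

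The cost is a revised sentence or two and slightly more analysis work. Patient codes and practice membership are already available, and no extra patients or data are needed.
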